### Outcomes

#### Primary outcomes

The primary outcome measures are treatment efficacy measured through PROMs according to the ESCP core outcome set of symptom reduction, subjective recurrences and complications (Table 1). The follow-up period for this outcome set is 6 months, and data will be collected at 4 different time points during this period (baseline, 1 week, 6 weeks and 6 months after the first procedure).

**Table 1 Tab1:** Primary and secondary outcome measures

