#### Treatment efficacy

This outcome follows the patient-reported outcome measure-haemorrhoidal impact and satisfaction score (PROM-HISS) questionnaire from the international Delphi procedure of the European Coloproctology group, for which recently the first steps in the validation process were taken [10, 11, 13].

This questionnaire consists of three domains: (1) HD symptoms, (2) impact of HD on daily activities, and (3) satisfaction with treatment [13]. The first domain contains five HD symptoms of which each is scored on a Likert scale ranging from 1 (“not at all”) till 5 (“very much”), resulting in a maximum possible score of 25. During follow-up, any reduction in score on this numeric scale is classified as ‘improvement’. This will then be translated into a binary outcome: “yes” or “no” improvement of symptoms. Both the second and third domains only contain one item, the impact of HD on daily activities and patients’ satisfaction with treatment, respectively. Both are scored on a 10-point numeric rating scale. In respect to the impact of symptoms on daily activities, 0 correlates with “no impact at all” and 10 with “highly impacted on daily activities”. On the contrary, for patient satisfaction with treatment, this ranges between 0 “not at all satisfied” and 10 “very satisfied”. Data from the PROM-HISS questionnaire is collected 1 week after the procedure, so the recall period comprises “the past week” [13].

Complications (i.e. incontinence, abscess, fistula, fissure, urine retention, anal stenosis, arterial bleeding or thrombosed haemorrhoid) are scored at the 6–8 week clinical follow-up appointment at the outpatient clinic. Subjective return of initial symptoms (recurrence) is recorded during the 6-month follow-up period.

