**Primary outcomes**				
HD symptoms (PROM)	X	X	X	X
Abscess			X	
Urine retention			X	
Anal stenosis			X	
Incontinence			X	
Fistula			X	
Recurrence			X	X

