### Sample size calculation

The sample size is based on a success percentage of 70% in both treatment arms, in terms of symptom reduction. Based on the available literature from Cocorullo et al. [6], we will perform a non-inferiority analysis with a two-sided significance (alpha 2.5%), 80% power and a 10% non-inferiority limit. Consequently, a total of 330 randomised patients are required per arm, so 660 randomised patients in total.Significance level (a) = 2.5%Power (1-beta) = 80%Non-inferiority limit = 10%Proportionality group A = 70%Proportionality group B = 70%Sample size required per group = 330Total sample size required = 660

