## Statistical analysis

Both intention-to-treat and per-protocol analyses shall be carried out. Crossover is not desirable, but possible if deemed necessary by the treating physician. Crossover will be considered as a secondary outcome measure. Analyses will be carried out using SPSS version 26.0. A *p*-value of 0.05 or less is considered as statistically significant.

For the primary outcome, any reduction in a PROM/PREM score per symptom is scored as ‘improvement’ when considering the results as binary success or not. Analysis of primary outcomes will be tested with chi-square test or Fisher’s exact test. Considering there are four time points for the outcomes, these time points will be taken into account during the analysis. Descriptive methods will be used to check the quality of the data, homogeneity of the two treatment groups and primary and secondary endpoints. Significant confounders will be identified using multivariate analysis. Categorical variables will be presented as percentages and continuous variables will be presented as means with their confidence intervals. To examine gender differences, an additional analysis will be carried out. An interim analysis will take place after the first 300 patients have been randomised and 6-month follow-up is completed. Both the number of patients who experienced complications and the number of patients with recurrent symptoms after 6 months will be evaluated between the two groups. If there are significant differences, then the entire study group will discuss these findings and discuss whether the study can be continued.

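### The tests named for the primary outcomes compare one yes/no result per patient, so they cannot combine the repeated follow-up readings, and no decisive time point or estimate against the 10-point margin is fixed

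*Protocol article*

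**What the plan says.** The outcomes section of the protocol article (Primary outcomes) gives a 6-month follow-up in which "data will be collected at 4 different time points during this period (baseline, 1 week, 6 weeks and 6 months after the first procedure". Table 2 places the symptom PROM at all four points. Under Treatment efficacy, any fall in the symptom score counts as improvement, and the result is reduced to yes or no.

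The Statistical analysis section then says: "Analysis of primary outcomes will be tested with chi-square test or Fisher’s exact test". The next sentence reads: "Considering there are four time points for the outcomes, these time points will be taken into account during the analysis". It names no method for doing this and no primary time point. The same section states: "Both intention-to-treat and per-protocol analyses shall be carried out".

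The design target stands in the Sample size calculation: "we will perform a non-inferiority analysis with a two-sided significance (alpha 2.5%), 80% power and a 10% non-inferiority limit", with 70% success in both arms and 330 patients per arm.

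**The concern.** The two sentences in the Statistical analysis section do not fit together. One fixes tests that take a single independent result per patient. The other promises to make use of several correlated readings from each patient. Baseline serves only to define improvement, so three follow-up results remain (4 - 1 = 3), each with its own table and p-value. Nothing says which of them decides the trial.

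The named tests also address whether the arms differ. The trial asks whether SCL is worse than RBL by no more than 10 points, and a chi-square p-value does not answer that.

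A further consequence is conditional. If a patient has no reading at a visit and no value is assigned, that patient is absent from the visit's table. Where absence is linked to poor response, the comparison shifts, and earlier scores that could help are not drawn on by tests of this kind.

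**Working it through.** **1. The design figure.** With 70% in both arms, a margin of 0.10, one-sided alpha 0.025 and 80% power:

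n = (1.960 + 0.842)² × 2 × 0.70 × 0.30 / 0.10² = 329.7, hence 330 per arm.

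This matches the article exactly. It contains no allowance for missing readings, and one-sided 2.5% is therefore the level used below.

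**2. What the named test can show about the margin.** At 70% and 330 per arm, SE = √(2 × 0.21 / 330) = 3.57 points, so the 95% half-width is 1.96 × 3.57 = 7.0 points. A chi-square test at 0.05 is non-significant for differences up to about 7.0 points. Non-inferiority needs an observed difference no worse than about -10 + 7.0 = -3.0. An observed deficit for SCL between about 3 and 7 points would thus be non-significant and still not non-inferior. (Approximate, because the SE changes slightly with the rates.)

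**3. What happens if patients without a reading drop out of the table.** The documents give no loss rates, so everything in this step except the 330 is assumed:

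- Improved at 6 weeks: q = 70% RBL, 60% SCL.
- 6-month success if improved / not improved at 6 weeks: a / b = 85% / 35% RBL, 80% / 30% SCL.
- True 6-month success: 0.7 × 0.85 + 0.3 × 0.35 = 70% RBL; 0.6 × 0.80 + 0.4 × 0.30 = 60% SCL. SCL is worse by exactly the margin.
- 6-month reading missing in 10% of improved patients and in a share u of unimproved patients.

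Formulas, per arm: retention r = 0.90q + (1 - q)(1 - u); observed success s = [0.90q·a + (1 - q)(1 - u)·b] / r; patients in the table = 330r. Then d = s(SCL) - s(RBL), SE is unpooled, and P(false non-inferiority) = 1 - Φ(1.96 - (d + 0.10)/SE).

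Worked case, u = 25% RBL and 40% SCL:

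- RBL: r = 0.63 + 0.225 = 0.855; s = (0.5355 + 0.07875)/0.855 = 0.718.
- SCL: r = 0.54 + 0.24 = 0.780; s = (0.432 + 0.072)/0.780 = 0.646.
- d = -7.2 points, SE = 4.01 points, P = 1 - Φ(1.96 - 2.77/4.01) = 0.102.

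| Unimproved patients missing, RBL v SCL | Observed success, RBL v SCL | Difference (points) | P(false non-inferiority) |
|---|---|---|---|
| 25% v 40% | 0.718 v 0.646 | -7.2 | 10.2% |
| 40% v 25% (swapped) | 0.739 v 0.621 | -11.7 | 0.8% |
| 35% v 35% | 0.732 v 0.638 | -9.4 | 3.5% |
| 10% v 10% (loss unrelated to status) | 0.700 v 0.600 | -10.0 | 2.5% |

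The calculation takes a confidence limit against -10 as the decision rule, because that is the design target. The Statistical analysis section does not itself name that rule.

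**The case against.** Four counter-arguments deserve weight.

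- **Separate tests are feasible.** Testing improvement at each follow-up visit is one ordinary reading of the sentence on time points. This stands: the plan can be executed. It then yields three p-values without a rule for which one counts, and it still does not combine the readings.
- **The article is silent on missing data.** A reader might infer that intention to treat here becomes a complete-case analysis. The documents do not support that. Chi-square and Fisher accept whatever binary values they are given, and missing results could be imputed or counted as failures beforehand. Such rules are commonly left to the full protocol or analysis plan, which are not shown, so their absence is no finding.
- **Drift towards non-inferiority is not established.** A reader might infer this too. It requires heavier loss of unimproved patients in SCL, and nothing in the documents suggests that. Patients not better at 6 weeks can receive a repeat treatment, which is a reason to stay in contact, and the 6-month reading needs only a telephone call. On the other side, patients know their treatment and may withdraw at any time, so loss that depends on arm and outcome cannot be excluded. Swapping the assumed rates reverses the bias.
- **The earlier readings are no guaranteed cure.** In the illustration, adjusting for 6-week status within arm returns -10 by construction, because loss was made to depend on that status alone.

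**Conclusion.** The point holds for what the article states. The tests fixed for the primary outcomes cannot combine the repeated readings that the next sentence promises to use. As written, they leave three per-visit comparisons, no decisive time point and no estimate against the 10-point margin. That part needs no assumption.

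The effect of missing readings is a conditional consequence. With true rates at the margin, the illustrated chance of false non-inferiority runs from under 1% to about 10%, depending on which arm loses more unimproved patients. It is 3.5% at 35% loss of unimproved patients in both arms and the nominal 2.5% when loss is unrelated to status. These figures rest on assumed loss and response rates and on patients without a reading being left out. They show that the result can be sensitive, and give neither a predicted size nor a direction. The change is worth making because it is cheap and settles the analysis before results are known.

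**What to change.** In the Statistical analysis section:

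1. Name one decisive time point for symptom improvement. Six months, the end of follow-up, is proposed; the article does not fix it, so the sponsor must choose it explicitly.
2. Make the primary analysis the risk difference in improvement (SCL minus RBL), with its confidence interval set against the 10-point margin, in all randomised patients as allocated.
3. Use the baseline, 1-week and 6-week PROM totals already collected, through multiple imputation within arm (available in SPSS), and derive improvement from the imputed totals. A repeated-measures binary model is an alternative. Either removes bias only so far as loss depends on the observed readings. State that improvement is judged on the total score, since Treatment efficacy uses the total while Statistical analysis speaks of each symptom.
4. Add one conservative sensitivity analysis that counts missing SCL patients as not improved and imputes missing RBL patients.
5. Report the 1-week and 6-week differences as supporting results, and keep chi-square and Fisher's exact test for descriptive tables.

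The cost is revised wording and some programming, with no new data. The interval will be slightly wider than one that ignores the missing readings.

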### Eligibility criteria

#### Inclusion criteria

Grade 1 (symptomatic with rectal blood loss) or grade 2 haemorrhoids (Golligher classification)Aged 18 years old or older and legally competent

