### Recruitment and blinding

In the Netherlands patients with HD are mostly referred to the surgeon by their general practitioner. The outpatient clinic nurses or researchers will screen for eligibility and send the patient written information (study information folder (PIF) and plan their appointment at the outpatient clinic. This allows for a minimum of 48 h to reflect on the information. The patient takes the information to the outpatient clinic appointment to discuss with the treating physician. In the case of participation, oral and written consent are gathered.The treating physician generates the allocation process or registration to the preference arm, after written informed consent has been provided.The randomization sequence will be computer generated with the Castor^EDC^ program (version 24.41) without stratification, with 1:1 allocation to either group, generating a unique record number.Both patient and treating physician are not blinded for the treatment arm.In concept, the researcher who completes the telephone interviews at 7 days and 6 months is blinded to the given therapy and is instructed not to actively ask patients which treatment they received. However, the data is added in the same database system, so complete blinding is not guaranteed. The physician at T = 0 and T = 6 weeks is not blinded as it is otherwise impossible to complete the treatment. Also, at 6 weeks the treating physician should repeat the initial treatment when necessary, following protocol.

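### The randomised comparison is left unadjusted beside an open search for significant confounders; a fixed covariate set would use baseline data already collected and settle which estimate leads

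*Protocol article*

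**What the plan says.** The Statistical analysis section of the protocol article gives the primary test: "Analysis of primary outcomes will be tested with chi-square test or Fisher’s exact test". No covariate enters it. The same section, just after a descriptive check that the two groups are comparable, adds: "Significant confounders will be identified using multivariate analysis". It names no candidate variables, no outcome for the model and no use for the result. The only threshold in the section is that a p-"value of 0.05 or less is considered as statistically significant".

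Under Recruitment and blinding, the allocation sequence is generated "without stratification, with 1:1 allocation to either group".

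Three obvious covariates are already recorded:
- **Baseline symptom score:** Table 2 schedules the PROM at baseline.
- **Grade:** it is part of the entry criteria, "Grade 1 (symptomatic with rectal blood loss) or grade 2 haemorrhoids".
- **Centre:** under Data collection, baseline and procedure data are gathered hospital by hospital.

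The article also describes a preference arm for patients who refuse randomisation (Trial design, Interventions). The confounder sentence is not limited to that arm.

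**The concern.** Looking for significant confounders suits a non-randomised comparison. Between the randomised arms there is no systematic confounding to find, because any baseline difference is due to chance. Covariates help there because they predict the outcome, and they can be named in advance. Choosing them by a p-value in the trial data, especially a p-value for baseline imbalance, tends to miss the useful ones.

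Baseline score is an obvious candidate. Success is a fall from that score, and Table 1 puts the scale's floor at 5, so a patient near the floor has little room to succeed.

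Two things are at stake. One is precision that the trial has already paid for and does not use. The other is hierarchy: an unadjusted test and an open-ended multivariable analysis stand side by side, and the article does not say which result prevails if they disagree about the 10% margin.

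**Working it through.** **Inputs from the article (Sample size calculation).** "The sample size is based on a success percentage of 70% in both treatment arms, in terms of symptom reduction"; "non-inferiority analysis with a two-sided significance (alpha 2.5%), 80% power and a 10% non-inferiority limit"; "a total of 330 randomised patients are required per arm, so 660 randomised patients in total".

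**Step 1: reproduce the plan's figure.** With 70% in each arm, the variance term is 2 × 0.70 × 0.30 = 0.42.

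n per arm = 0.42 × (1.960 + 0.8416)² / 0.10² = 0.42 × 7.849 / 0.01 = 329.7, rounded up to 330.

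This matches exactly for an unadjusted difference at one-sided 2.5%. A literal two-sided 2.5% (1.25% in each tail) would need 400 per arm; that labelling is a separate matter.

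**Step 2: power of the unadjusted comparison.** SE = √(0.42/330) = 0.0357. Power = Φ(0.10/0.0357 − 1.960) = 80.0%. There is no shortfall against the plan.

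**Step 3: effect of a fixed covariate set.** If the covariates explain a share R² of outcome variance, the variance of the difference is multiplied by (1 − R²):

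SE = √(0.42 × (1 − R²)/330); power = Φ(0.10/SE − 1.960).

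The documents give no R², so the values below are assumptions shown as a range.

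| Assumed R² | SE | Power at 330 per arm | n per arm for 80% |
|---|---|---|---|
| 0 | 0.0357 | 80.0% | 330 |
| 0.05 | 0.0348 | 82.0% | 314 |
| 0.10 | 0.0338 | 84.0% | 297 |
| 0.20 | 0.0319 | 88.0% | 264 |

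**Step 4: simulation of the selection rules.** Each scenario had 660 patients, 2,000 runs, 70% success in the reference arm and 10 centres (assumed). Adjusted estimates were standardised risk differences from a logistic model. The two selection rules chose at the 5% level from baseline score, grade and six irrelevant variables; only the fixed set included centre. Monte Carlo error is about √(0.8 × 0.2/2000) = 0.9 points for power and √(0.025 × 0.975/2000) = 0.35 points for the error rate.

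| Power when the arms are equal | R² ≈ 0.03 | R² ≈ 0.11 | R² ≈ 0.23 |
|---|---|---|---|
| Unadjusted | 79.5% | 79.5% | 78.0% |
| Fixed set | 80.7% | 83.4% | 88.7% |
| Selected on association with outcome | 80.7% | 82.2% | 87.8% |
| Selected on baseline imbalance | 79.2% | 80.0% | 79.1% |

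With a true difference at the −10 point margin, the one-sided error was 2.0–2.6% under every single rule. It was 3.1–3.8% when the most favourable of the unadjusted, outcome-selected and fixed-set results was taken, with an upward bias of 0.3–0.8 points.

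So selecting on outcome costs about 0–1 point of power against the fixed set, while selecting on imbalance loses nearly all the gain. The error rate rises only when there is freedom to choose among analyses.

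**The case against.** The strongest reply is that the primary test is unadjusted and an unadjusted randomised comparison is valid. The sample size was computed for one, and no stratification factor has to be carried into a model. The confounder sentence says only that variables will be identified, and it sits among descriptive checks. Covariate lists and model form usually belong in an analysis plan, which is not shown. Most of this stands, and it limits the point in four ways.

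- A reader might infer that the primary treatment estimate becomes data-driven. The article does not say that selected confounders enter or replace the primary result, so this can apply only to a further adjusted estimate.
- A reader might infer that selection inflates the false-positive rate. Selection alone did not do so in the simulation. The rise to 3.1–3.8% needs someone to report the best of three analyses, which the article does not plan.
- A reader might infer that unstratified allocation biases the comparison. It does not: chance imbalance in grade or centre is already reflected in the interval. It only means that the design secures no balance that adjustment could not improve upon.
- A reader might want the sentence deleted. Control of confounding is legitimate for the preference cohort, so it should be confined, not removed.

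The reply fails on one count. The sentence is not an omission left to another document. It states a rule, and an analysis plan that named a fixed covariate set as the sole basis for adjustment would conflict with it as written.

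**Conclusion.** The point holds as an improvement available at almost no cost, not as an error that invalidates the trial. The significance-based search is badly suited to the randomised comparison, is not confined to the preference arm, and has no stated rank against the unadjusted test. Lack of adjustment costs the plan none of its stated 80% power; what is forgone is extra precision. On assumed R² values of 5%, 10% and 20%, that is about 2, 4 and 8 percentage points of power at 330 per arm. If the covariates predict little, the gain is about one point (simulation at R² ≈ 0.03). These figures rest on 70% success in both arms, a 10-point margin, one-sided 2.5% and full follow-up of 330 per arm. Whether the chi-square test itself addresses the non-inferiority margin is a separate question and is not settled here.

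**What to change.** 1. Limit the confounder search to the preference cohort, or label it exploratory.
2. For the randomised comparison, pre-specify as primary a covariate-adjusted risk difference with 95% confidence interval, read against the 10% margin. Obtain it as a marginal (standardised) estimate from a logistic model.
3. Fix the covariates in advance: baseline PROM score, haemorrhoid grade and centre, with a stated rule for pooling small centres. Use the baseline score that matches the definition of success, because Treatment efficacy refers to the summed scale and Statistical analysis to each symptom.
4. Use as a covariate only baseline scores obtained before the patient knows the allocation. Table 2 allows baseline to be taken at allocation or by telephone, and patients are not blinded. State how a later or missing score is handled in the model, without reference to arm.
5. Report the unadjusted difference as a sensitivity analysis, and state that the adjusted estimate decides.

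Date the change before any outcome is compared between arms, including at the interim analysis. The cost is a change of wording and slightly more analysis work: no new data, no extra patients and no change to the sample size.

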## Introduction

### Background and rationale

Haemorrhoids are a part of normal anatomy, and yet the term haemorrhoids is often used to refer to haemorrhoidal disease (HD) in which clusters of vascular tissue, smooth muscle and connective tissue in the anal canal give rise to symptoms of blood loss, itchiness, soiling and/or prolapse [1]. HD is a common condition with significant epidemiologic and economic relevance. The prevalence of HD rises up to 55% for adults aged between 45 and 65 years of age, with an annual incidence of 5% of the general population [2].

In 1985, Goligher was the first to report a widely accepted grading system for haemorrhoids, which describes four separate groups based on the extent of prolapse inside, or outside, the anal canal [3]. In 460 B.C., Hippocrates described HD with a plethora of treatments, varying from burning, herbs, ligation and surgical excision [4]. Currently, various treatments are available to treat HD [5, 6].

Symptomatic grade 1–2 haemorrhoids can be treated with either rubber band ligation (RBL) or sclerotherapy (SCL) and both treatment options often require multiple sessions [6]. The most common symptom for this patient population is rectal blood loss accompanying defecation [3, 7]. RBL is based on the strangulation and necrosis of haemorrhoidal tissue, resulting in fibrosis and fixation to the surrounding anal mucosa [5, 8]. The most important disadvantages are the feeling of urgency, pain and soiling during and after the procedure. A rare but serious complication of RBL is the occurrence of an arterial bleeding, which in some cases needs to be stopped surgically. On the contrary, SCL induces an inflammation process and local sclerosis of the submucosa which initiates fixation of the haemorrhoidal tissue to the anorectal wall [6, 8]. The haemorrhoid shrinks through the obliteration of the vascular wall. Current literature does not describe major negative side effects, with only a few cases of local infection and haemorrhoidal thrombosis, and very rare complications such as fistula formation and impotence [6, 8]. In the event of haemorrhoidal thrombosis, oral pain medication is usually sufficient; surgical incision of the clot is scarcely required. Another agent that is used in the treatment of HD is phenol. A study showed that it can be equally effective as Aethoxysklerol; however, the use of phenol led to more adverse reactions such as pain, necrosis and ulceration [9].

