### Data monitoring

The THROS trial is monitored internally by the Scientific Office of the Flevoziekenhuis in cooperation with the hospital quality and safety department. All participating centres also ensure monitoring standards. Any serious complications must be reported as soon as possible to the coordinating researchers who will report this to the chairman of the Scientific Office. No external data monitoring committee has been established because the interventions included in this trial are low-risk interventions and have been used in the participating centres for a significant amount of time (i.e. > 10 years). The principal investigator will update the Medical Ethics Committee on the status of the investigation once a year. An estimation of the degree to which the study objectives are reached, the reporting of adverse events, and other reports that may be relevant for the assessment of the investigation's progress are all included in the yearly progress report.

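### The only stated between-arm look at harm waits for 6-month follow-up, after complications are scored at 6–8 weeks, and its significance trigger is very unlikely to pick up a rare serious imbalance

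*Protocol article*

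**What the plan says.** All references are to the protocol article.

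- **Timing of the interim** (Statistical analysis): "An interim analysis will take place after the first 300 patients have been randomised and 6-month follow-up is completed".
- **What is compared** (same section): "Both the number of patients who experienced complications and the number of patients with recurrent symptoms after 6 months will be evaluated between the two" (that is, the two arms).
- **Trigger** (same section): "If there are significant differences, then the entire study group will discuss these findings and discuss whether the study can be continued". No separate interim significance level is given. The section's general rule is that a p-"value of 0.05 or less is considered as statistically significant".
- **When complications are recorded** (Treatment efficacy): they "are scored at the 6–8 week clinical follow-up appointment at the outpatient clinic". The list there includes arterial bleeding. Table 2 marks the complications that it lists at the 6-week visit only, and Data collection also places the scoring at that visit. Recurrence is recorded up to 6 months.
- **Oversight** (Data monitoring): "No external data monitoring committee has been established", on the ground that both treatments are low-risk and long established at the centres. Serious complications go promptly to the coordinating researchers and then to the chair of the Scientific Office. Under Risk of harms, all SAEs go to the ethics committee, with a safety report once a year.
- **A named asymmetric risk** (Background and rationale): "A rare but serious complication of RBL is the occurrence of an arterial bleeding, which in some cases needs to be stopped surgically". No rate is given.

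**The concern.** Two features of the interim limit its use as a safety check.

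The first is timing. The complication comparison is tied to the 6-month clock that recurrence needs. The scheduled complication data on the first 300 patients are in hand about four months sooner, and the article mentions no pause in recruitment while the rest of the follow-up runs.

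The second is the trigger. Discussion depends on a significant difference in a count of patients with complications. A fissure and an arterial bleed that needs surgery weigh the same in that count, and a rare event adds little to it. With no external committee and no stated by-arm review of the serious-event reports, this is the only stated point before the end at which harm is compared between arms. An imbalance in a serious event might not prompt the discussion that the plan intends, and patients would go on being randomised meanwhile.

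**Working it through.** **The plan's own figure.** The article gives no power or boundary for the interim. Its one calculated figure, 330 per arm, reproduces with a one-sided alpha of 2.5%: n = (1.960 + 0.842)² × 2 × 0.70 × 0.30 / 0.10² = 329.7, rounded up to 330, so 660 in total. Nothing below changes it; 660 serves only as a cap on accrual.

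**Inputs for the trigger.** 300 patients at 1:1 allocation give about 150 per arm. The threshold is p ≤ 0.05. The tests are chi-square or Fisher's exact, as named for the primary outcomes, which include complications.

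**1. A serious event tested on its own, none in the other arm.**

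Two-sided Fisher, k v 0: p = 2 × C(150,k)/C(300,k).

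- k = 5: 2 × (150/300)(149/299)(148/298)(147/297)(146/296) = 0.060
- k = 6: multiply by 145/295, giving 0.030

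Uncorrected chi-square, k v 0: X² = 300 × (150k)² / [k(300 − k) × 150²].

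- k = 3: 3.03, p = 0.082
- k = 4: 4.05, p = 0.044

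The first significant split is therefore 6 v 0 (4% of one arm) by Fisher, or 4 v 0 by chi-square. Exact power by binomial enumeration:

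| True rates | Fisher | Chi-square |
|---|---|---|
| 1% v 0% | 0.4% | 6.5% |
| 2% v 0% | 8% | 35% |
| 3% v 0% | 30% | 66% |
| 5% v 0% | 77% | 95% |

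**2. The count of patients with any complication.** Assume the same background rate b in both arms and an independent serious event at rate s in one arm. That arm's rate is b + (1 − b)s. For b = 34% (the lower end of the published sclerotherapy range in the Introduction) and s = 3%, this is 0.34 + 0.66 × 0.03 = 0.3598, a difference of 1.98 points. The standard error is √(2 × 0.350 × 0.650/150) = 5.5 points, so the true difference is about 0.36 standard errors, where 1.96 are needed. Exact chi-square power:

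| Background | s = 2% | s = 3% | s = 5% |
|---|---|---|---|
| 10% | 8% | 11% | 22% |
| 34% | 5.5% | 6.4% | 9.0% |

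At 34% this is close to the 5% false-positive rate. The count reaches 80% power only for differences of about 12 points (from 10%) to 16 points (from 34% or 49%).

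**3. Timing.** No accrual rate is given, so a range is assumed. The number randomised at the look is 300 + r × delay, capped at 660, for r patients a month. The delay is 6 months, or 8 weeks = 8/4.345 = 1.84 months.

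| r per month | At 6 months | At 8 weeks | Difference |
|---|---|---|---|
| 5 | 330 | 309 | 21 |
| 10 | 360 | 318 | 42 |
| 20 | 420 | 337 | 83 |
| 40 | 540 | 374 | 166 |
| 55 | 630 | 401 | 229 |

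At 60 a month or more, all 660 are randomised before the planned look.

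**The case against.** **Complications do not end at 6–8 weeks.** A reader might infer from the scoring schedule that they are final by then and that the complication look can simply be moved forward. The article does not support that. Outcomes gives the primary outcome set, complications included, a 6-month follow-up. Interventions and Participant timeline allow a repeat treatment at the 6–8 week visit and a later crossover, and the Discussion expects repeat procedures in most cases. This stands, and it shapes the remedy: an early look must be added, because moving the only look would leave events after retreatment out of the interim.

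**Serious events are not unseen.** A reader might also infer that they go unnoticed or could never be discussed. Data monitoring and Risk of harms provide prompt and yearly reporting, and the treating physician is not blinded. This also stands. What is left is narrower: no stated step sets those reports side by side by arm.

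**The count may not be the whole interim.** Table 1 lists the complications separately, the article condenses a fuller plan, and a breakdown by type is not excluded. That is fair as to table layout. But the article itself fixes the timing, the quantity compared and the condition for discussion. A breakdown tested for significance would still need 6 v 0 or 4 v 0.

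**Lateness is not established.** It cannot be said that the look necessarily comes after most patients are enrolled: at 10 a month, 300 are still to be randomised. The Discussion mentions two haemorrhoid trials stopped early for inclusion difficulties, so slow accrual is plausible. An 8-week look would itself come with 309 to 401 of 660 randomised (47% to 61%). The gain is real but may be small.

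**The interventions are low-risk.** This justifies light monitoring and lowers the urgency. It does not explain why complication data already collected should wait for recurrence data.

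**Conclusion.** The point holds as a worthwhile improvement to safety monitoring. It does not affect the sample size or the main analysis.

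- The planned between-arm comparison of complications comes about four months after their last scheduled scoring in the first 300 patients.
- Its significance trigger is very unlikely to respond to a rare serious imbalance. Power is about 6% for an extra 3% of serious events in one arm on a 34% background, and 11% on a 10% background. These figures assume equal backgrounds, independence of serious and other complications, and p ≤ 0.05. For a serious event tested alone, the chance of a significant result depends strongly on the test used and becomes substantial only from about 3% to 5% in one arm.
- The delay means about 20 to 230 more patients randomised before the look, for an assumed 5 to 55 a month.

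**What to change.** 1. Add a complication review when the first 300 randomised patients have completed the 6–8 week visit. Tabulate each complication type and each SAE by arm.
2. State that the study group will discuss an imbalance in serious events at that review without requiring a significant p-value.
3. Keep the planned 6-month interim for recurrence, and update the complication and SAE tables there so that events after repeat treatment or crossover are included.

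The cost is one extra data cut, one extra interim report and a change of wording. No patients or visits are added. The second step relies on judgement rather than a numerical boundary, which suits events too rare to test.
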